## Abstract

Attention training is the primary step in the rehabilitation for patients with acquired brain injury (ABI). While active music performance has been reported to aid neural and functional recovery, its efficacy for patients with ABI remains uncertain due to methodological concerns. The purpose of the study is to develop a virtual reality-based music attention training (VR-MAT), which utilizes a visually guided, bilateral drumming in an immersive environment to train attention and executive functions. We also aims to examine the feasibility and effectiveness of the VR-MAT with a small sample size of participants (3–60 months after ABI, *N* = 20 approximately). Participants will be randomly assigned to either a waitlist control or music group, in which VR-MAT will take place five times weekly over 4 weeks (randomized crossover design). The evaluation of VR-MAT performance will include accuracy and response time in music responses. Neurocognitive outcome measures will be administered to quantify pre-post changes in attention, working memory, and executive functions. Additionally, functional near-infrared spectroscopy will be employed to explore the relationships between musical behavior, neurocognitive function, and neurophysiological responses.

## Introduction

1.

Acquired brain injury (ABI) is the damage to the brain that occurs due to certain events after birth (1) and includes traumatic injury and/or stroke (2, 3). Many individuals with ABI experience temporary or permanent neurological sequelae which is not limited to psychomotor, cognitive, and communication difficulties (4–7). The prevalence of ABI-related changes in cognition, including attention, working memory, memory, and executive function, is high (8–12), leading to a lower quality of life, accelerated functional decline, and a higher risk of dependence and mortality (5, 7). Cognitive impairments can decrease therapeutic potential and clinical benefits, since verbal and non-verbal information given in therapeutic settings is hardly recognized. Attention impairment should be a priority in the rehabilitation agenda for patients with ABI because dysfunctions in the fundamental mechanism of attention are pervasively involved in cognitive impairment (13–19). More importantly, auditory attention appears to be more challenging in patients with ABI (20, 21). These patients often have difficulty attuning their attention to relevant auditory information and distinguishing target sounds from distracting sounds (20, 22–24).

Auditory information processing is challenging because it is both sequential and simultaneous. Listening to music can enhance attentional function, which is required to process complex auditory information. Music automatically activates the attention system, even when actively ignoring presented melodies and voluntarily attending to target melodies (25). In addition, music processing in different textures can lead to activation in neural regions that house different types of attention, such as selective attention and divided attention, depending on the manner of listening to music (i.e., holistic, selective, or divided) (26–28). Music error/change detection tasks can be utilized to investigate and train auditory attention (26, 29–33). More recently, active music performance and listening have been applied to cognitive rehabilitation. An initial study investigated the effects of a music attention training program on five adults with TBI (34), which was developed based on a hierarchy of attention (35). Furthermore, one study examined the effect of a music attention training program on alternating attention using a dichotic listening test (36), and another study suggested that music therapy is an effective early intervention for cognitive rehabilitation (37).

More recently, active music performances have been applied to various populations, such as juveniles, adolescents with neurodevelopmental disorders, and psychiatric patients. Abrahams and van Dooren (38) compared music attention control training (MACT) with non-standardized music therapy (NSMT) and treatment as usual (TAU) in terms of the attentional ability of juveniles (*N* = 6). With a six-week training of 45 min weekly, some participants in the MACT group showed an extensive increase in selective, sustained, and divided attention. Pasiali et al. (39) investigated the effect of the MACT on the attentional function of adolescents with neurodevelopmental delays using a single-group pre-and post-test design. With a six-week training of 45 min weekly, participants showed considerable improvements in selective attention and divided attention. van Alphen et al. (40) conducted a randomized controlled trial to determine the effect of MACT on attention skills in a group of adult psychiatric patients. After a 6 week training of 30 min weekly, single-blind pre-and post-intervention showed a marked enhancement in selective, sustained, and alternating attention in the MACT group. Jones (14) conducted a randomized controlled trial (RCT) to examine the effect of MACT compared to that of Attention Process Training (APT). The findings showed significant values and partial support from nonparametric testing, suggesting the potential of MACT in favor of APT.

Despite rigorous attempts, the efficacy of active music performance for patients with ABI is still under debate. For instance, in a systematic review of music and rehabilitation, Bradt et al. (41) reported that psychomotor rehabilitation effectively improves gait regulation, yet the success of cognitive rehabilitation remains uncertain. Similarly, Magee et al. (42) provided evidence supporting the positive influence of music interventions on upper and lower mobility functions as well as speech. Nonetheless, only two studies (43, 44) demonstrated the efficacy in music-based cognitive rehabilitation. Both reviews agreed on the urgent need for high-quality RCTs focusing on cognitive rehabilitation, along with a lack of replicable therapeutic protocols for music-based training designed to aid recovery from cognitive deficits (34, 36, 45). Most studies relied solely on functional outcome measures without quantifying musical responses, potentially missing key relationships between musical and functional behaviors, as well as changes uniquely evident through musical behaviors. To address the limitations, we developed a replicable therapeutic protocol of active music performance and integrated the protocol with a virtual reality system. The efficacy of VR-MAT will be evaluated through randomized cross-over trials, using a comprehensive data collection strategy that incorporates neuropsychological, neurophysiological and music responses measures.

## Materials and methods

2.

### Study design

2.1.

The present study will be conducted as an assessor-blinded, randomized, controlled trial with a crossover design at a rehabilitation hospital. Participants will be randomly allocated to either the treatment sequence: VR-MAT first and second with conventional cognitive training (CT) (VC group), or in the opposite order (CV group) with an allocation ratio of 1:1 using a computer-generated randomization table. The crossover design is selected because the participants need to serve as their own control group to minimize confounding effects on cognition, which might be markedly affected by a person’s traits, which is not intended by the intervention. In addition, it might be beneficial for the statistical efficiency of this pilot trial, in which VR-MAT had not been attempted for patients with ABI.

Each VR-MAT or CT training period will last 4 weeks with five 30-min intervention sessions per week, resulting in a total of 20 sessions. Therefore, each participant will have received a total of 40 sessions of the intervention, comprising 20 sessions of VR-MAT and 20 sessions of CT. The randomized group assignments were concealed in consecutively numbered sealed opaque envelopes placed in a plastic container. The allocated group will then be determined by the sequential opening of the envelopes after obtaining written informed consent from the participants. Participants will receive a conventional inpatient rehabilitation program (1 h of physical therapy or 30 min of occupational therapy); however, they will not receive a cognitive intervention. Outcome measurements will be performed by a researcher blinded to the group assignment.

### Participants

2.2.

Participants will be recruited among patients who have been admitted to the neurorehabilitation unit of the rehabilitation hospital. The inclusion criteria are as follows: (1) cognitive impairment secondary to a first-ever ABI, as evidenced by a Clinical Dementia Scale (CDR) score of 0.5 – 1; (2) a diagnosis of ABI > 3 months ago with medical records and/or brain imaging; (3) no history of prior ABI; (4) upper limb muscle strength of ≥ 3 on the medical research council scale, indicating suitability for training and assessment; (5) age >19 years. The exclusion criteria are: (1) known cognitive impairment prior to ABI; (2) severe aphasia or cognitive communication disorder precluding cognitive intervention, including MAT and CCT, or assessment; (3) neurological or psychiatric disorders other than ABI; (4) severe depression (Geriatric Depression Scale-short form score of ≥8); (5) uncontrolled medical illnesses, such as severe cardiac or respiratory disease. The exclusion criteria are as follows: (1) known cognitive impairment prior to ABI; (2) severe aphasia or cognitive communication disorder which precluded cognitive intervention including MAT and CCT or assessment; (3) neurological or psychiatric disorder other than ABI; (4) severe depression [Geriatric Depression Scale-short form ≥8]; (5) uncontrolled medical illness such as severe cardiac or respiratory disease. The experimental protocol was approved by the ethics committee of the rehabilitation hospital (IRB no. NRC-2015-04-032). Sample size calculation was not possible because the effects of the VR-MAT on cognitive function have not yet been reported. Therefore, we have set the sample size to 12 for each arm, in accordance with the minimum number recommended for pilot trials (46, 47). In total, considering a potential participant attrition rate of 20%, we aim to recruit 24 participants for this pilot study.

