### Statistical analysis

2.7.

We will perform descriptive statistical analysis of the general demographics of the study participants. We define completers as participants who finish 20 sessions of either intervention (VR-MAT or CT) and undergo measurements at 4 weeks of intervention. The statistical analysis will be conducted on an intention to treat basis and the last observation carried forward method will be used to complete the data. Adherence will be reported as the number of completers among enrolled participants. For neuropsychological assessments, a comparative analysis between two different intervention sequences (VC or CV) will be performed and the carry-over effects will be tested using *t*-tests on the change in each sequence for all crossover endpoints (70, 71). For variables with insignificant carry-over effects, the changes in variables during specific interventions from either sequence will be combined and compared. For patients with significant carry-over effects, we will compare the changes in specific interventions during the first period (20 sessions of either intervention). Comparisons between interventions will be performed using a two-tailed *t*-test or the Mann–Whitney *U* test, depending on normality. For music behavior responses obtained from the VR-MAT data, we will perform a two-way repeated-measures analysis of variance (ANOVA) on level (levels 1, 2, 3, and 4) and time (pre, day 8, day 15, and post) with Bonferroni *post-hoc* comparisons.

Repeated measures of correlation between executive function assessment and VR-MAT variables will be examined to determine the linear relationship between paired repeated data using the R package rmcorr from R.3.6.1 (72). The independent variables will remain the same for the analysis of fNIRS data, and the dependent variables will be the PRIs obtained from all channels. All analyses will be performed using the software package R.3.6.1,^1^ and the level of significance will be set to 0.05.

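### Section 2.2 presents the target of 24 as allowing for 20% attrition, but 24 is 2 × 12 with no inflation; about 19 (9–10 per sequence) would be expected to complete

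*Protocol article*

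**What the plan says.** Section 2.2 (Participants) explains that no formal calculation was made: "Sample size calculation was not possible because the effects of the VR-MAT on cognitive function have not yet been reported". It then fixes the size by convention: "we have set the sample size to 12 for each arm, in accordance with the minimum number recommended for pilot trials". The next sentence gives the recruitment target: "In total, considering a potential participant attrition rate of 20%, we aim to recruit 24 participants for this pilot study".

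Section 2.1 (Study design) has two treatment sequences, VC and CV, "with an allocation ratio of 1:1 using a computer-generated randomization table". The abstract gives N as "20 approximately".

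Two statements in section 2.7 (Statistical analysis) bear on what attrition means here. Completers are defined: "We define completers as participants who finish 20 sessions of either intervention (VR-MAT or CT) and undergo measurements at 4 weeks of intervention". Dropouts stay in the analysis: "The statistical analysis will be conducted on an intention to treat basis and the last observation carried forward method will be used".

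**The concern.** The two sizing sentences in section 2.2 follow one another. The first gives 12 per arm. The second says that 20% attrition has been considered and arrives at 24. A reader will take 24 as a number that already includes a margin for dropout, but it is the uninflated total.

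This matters because the recommended pilot minimum is the only basis the protocol gives for its size. As written, a reader may believe that about 12 per sequence will still be there at the end. On the protocol's own attrition rate the expected number is 9–10. The abstract's figure of about 20 adds to the uncertainty, because it is not stated whether it means recruited, randomised or completing.

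**Working it through.** **Inputs (all from the protocol article)**
- Size per arm: 12 (section 2.2)
- Sequences: two, allocated 1:1 (section 2.1)
- Attrition: 20% (section 2.2)
- Recruitment target: 24 (section 2.2)
- Approximate N: 20 (abstract)

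**1. Reproducing the target.** With no attrition, 2 × 12 = 24. This is the stated figure exactly.

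**2. Applying the stated attrition to 12 per arm.** The usual inflation is n/(1 − d).
- Per sequence: 12/(1 − 0.20) = 15
- Total: 2 × 15 = 30

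The looser form n × (1 + d) gives 24 × 1.20 = 28.8, so 29 in total. Per sequence it gives 12 × 1.20 = 14.4, rounded up to 15, so again 30. Neither form gives 24.

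**3. Working forward from 24 recruited.**
- Total expected to complete: 24 × (1 − 0.20) = 19.2
- Per sequence: 12 × 0.80 = 9.6

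**4. Starting from the abstract's figure.**
- 20 × 1.20 = 24
- 20/0.80 = 25
- Attrition implied by 20 remaining out of 24: 1 − 20/24 = 16.7%

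So 24 can be reached from 20 by the looser form, and nearly by the usual one. The number protected would then be 20/2 = 10 per sequence, not 12.

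**5. Effect on precision, first-period comparison only.** Where carry-over is significant, section 2.7 compares the two interventions in the first period, which is a parallel-group comparison. The 95% half-width in SD units is t × √(2/n), with n per sequence.
- n = 12: t(22) = 2.074, and 2.074 × √(2/12) = 0.85 SD
- n = 9.6: t(17.2) = 2.108, and 2.108 × √(2/9.6) = 0.96 SD

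These values count only participants with observed outcomes. They do not apply to the pooled crossover comparison.

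**The case against.** **The 12 may mean randomised.** Section 2.2 never says that 12 per arm must remain after attrition. Whether the cited recommendation concerns those randomised or those evaluable cannot be settled from the article. If it concerns those randomised, 24 meets it. This stands, and it rules out a stronger conclusion that a reader might draw: that the trial falls below its own minimum. On this reading, however, the attrition clause does nothing to the target and should not be worded as though it did.

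**The abstract's 20 may be the expected number remaining.** It is close to 19.2, and 20 × 1.20 = 24. A reader might take it as a further, conflicting sample size, but the text does not establish that. On this reading 24 does contain an allowance, though over 10 per sequence, while section 2.2 argues from 12.

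**Analysis by intention to treat with last observation carried forward keeps 24 in the analysis.** That holds for the nominal number, but it adds no observed outcomes. A participant lost before week 4 has only a baseline value to carry forward, which gives an imputed change of zero.

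**The main comparison is the crossover one.** Where carry-over is not significant, changes under each intervention are pooled across sequences. Treating those changes as unpaired, the half-widths are about 2.013 × √(2/24) = 0.58 SD with 24 changes per intervention and 2.027 × √(2/19.2) = 0.65 SD with 19.2. The 0.85 and 0.96 SD values would overstate the imprecision of that analysis, so they belong to the first-period fallback alone.

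**Nothing quantitative depends on 24.** The protocol claims no power, effect size or precision, and it does not say that the pilot will be used to size a later trial. A reader might infer damage to either, but the document gives no basis for it.

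**Conclusion.** The point holds in a limited form. Section 2.2 presents 24 as allowing for 20% attrition, and no standard inflation of 12 per arm gives 24; the figure is the uninflated 2 × 12. At the stated rate about 19 would complete, 9–10 per sequence. Keeping 12 per sequence would take 30 participants, 6 more than planned. Each alternative reading still leaves something to correct: either the attrition clause has no effect, or the allowance rests on 10 per sequence and disagrees with section 2.2.

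The expected numbers assume that the 20% applies equally to both sequences and describes loss before completion. Section 2.2 does not tie the rate to a time point, and the completer definition in section 2.7 requires only one 20-session intervention and the week-4 measurement. If the 20% refers to loss by then, fewer may contribute both periods.

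This is a correction to the stated justification that should be made. It does not show that the pilot is too small for its purpose.

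**What to change.** Replace the two sizing sentences in section 2.2 with wording such as: *24 participants will be randomised (12 per sequence, the recommended minimum taken as the number randomised); at 20% attrition about 19 (9–10 per sequence) are expected to complete.* Remove any implication that 24 already includes a margin for dropout.

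In the abstract, replace the approximate N with 24 randomised and about 19 expected to complete.

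The cost is one rewritten statement in section 2.2 and one figure in the abstract, with no extra participants and no change of design. If the sponsor intends 12 completers per sequence instead, the target has to be 30 (15 per sequence), at the cost of 6 more participants. That choice is the sponsor's, but the text should state which is meant.

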### Virtual reality-based music attention training

2.3.

VR-MAT comprises virtual reality-based, visually guided, bilateral drumming on electronic instruments. The VR-MAT is designed to fit individual therapeutic sessions and employs the patients’ preferred songs given in a multisensory environment (i.e., visual, auditory, and haptic). The VR-MAT consists of evaluation and training sessions. The VR-MAT-Evaluation includes baseline tempo and visuomotor response assessment tasks, aiming to ascertain individual variations, providing baseline information for VR-MAT-Training. In the baseline tempo assessment, participants will be asked to play the drums at a comfortable tempo for 10 s using their dominant and non-dominant hands independently. The baseline tempo assessment will be repeated thrice. Once the baseline tempo of the patients’ drumming is calculated, the participants will be asked to play a visually cued rhythmic pattern on the given electronic drum. The rhythm patterns will consist of four-beat rhythmic patterns with a binary meter, representative of four popular music genres, Rock, Swing, Shuffle, Bossa-Nova. Each genre will encompass rhythmic patterns that vary in the level of difficulty. Figure 1 presents examples of rhythm pattern varied across difficulty level within the Rock genre. Visual cues will be presented at a comfortable tempo via flashes on a computer screen, positioned 70–80 cm in front of the patients. In the VR-MAT-Evaluation, we will also collect information about participants’ previous musical experiences, including years of music training, types of musical activities they have participated in, and their musical preferences.

**Figure 1 fig1:**
[figure not shown]
Examples of rhythm pattern across difficulty level.

VR-MAT-Training consists of four levels of visually guided drumming tasks designed to restore various attention types in a hierarchical manner: (1) MAT-Level 1: One hand drumming, (2) MAT-Level 2: Two hand drumming, (3) MAT-Level 3: Reversed drumming, and (4) MAT-Level 4: Alternating drumming. In VR-MAT Training Level 1, a four-beat rhythm pattern is visually presented on the computer screen, first on the left side, and then independently on the right side. In VR-MAT Training Level 2, the visual cues used in Session Level 1 are combined and presented concurrently. VR-MAT-Training Level 3 is a two-hand drumming task that employs reversed rhythm patterns compared with those used in Level 2. For example, the visual patterns presented on the right side are presented on the left side and vice versa. Because individuals already possess habituated body patterns, they must inhibit previously learned patterns while learning new reverse patterns. Finally, VR MAT Training Level 4 provides the rhythm patterns of Levels 2 and 3 in a randomly alternating manner. Each task includes 20–21 trials, and the completion time is approximately 40 min.

Given the nature of bilateral drumming, the VR-MAT utilizes a familiar four-beat rhythmic pattern with a binary meter. Rhythmic patterns are carefully designed to vary the level of difficulty based on the VR-MAT-Evaluation results. Background music (BGM), originally composed of a binary meter, is selected from the patient’s preferred song list. The BGM can be played by a therapist or recorded without a vocal track. In both cases, adjustment of the BGM tempo is necessary to maintain the baseline tempo of the patients. With the auditory feedback (either a kicking or snaring drum sound), three types of visual cues are given: (a) if the drum stroke is falling within a time range of ±150 millisecond, a flashlight is given (i.e., matched), (b) if the drum stroke is hit earlier than the exact target point, ranging between −300 to −150 millisecond, the ball is exploded (i.e., mismatched), (c) if the ball is missed in the time range mentioned above, no visual cue is presented (i.e., unmatched). Figure 2 shows the user interface of VR-MAT, and Figure 3 presents example rhythm patterns for each of the four training levels.

**Figure 2 fig2:**
[figure not shown]
User interface of VR-MAT. **(A)** The first page of the UI includes four sections; User ID input, Warm-up exercise (BPM check, Free ball drumming), Day, and BPM selection; **(B)** The second page of the UI includes selection of trials and levels.

